### Recruitment of general practices

General practices will be recruited from throughout England and Wales. We will use a database of practices in Wales, and a number of UK Clinical Research Network primary care local research networks to contact practices in a wide range of regions. Recruited practices are asked to sign a Study Agreement. Practices can have one or more participating clinicians (general practitioners, nurse practitioners, or practice nurses), however each participating clinician must consult regularly with children presenting with acute illnesses. All clinicians in the same practice are allocated to the same trial arm.

### Randomisation

Recruited practices will be randomised using block randomisation stratified by list size, antibiotic prescribing rate, and country (Wales or England). Each recruited practice will provide a list size which is compared to the mean for England and Wales. Antibiotic prescribing rates (antibacterial items prescribed per 1000 registered patients for 2005) for each practice will be obtained and these will be compared with the mean rate for each country. For each of the eight strata the study statistician will create a randomisation table using random permuted block sizes. These tables will be kept securely and allocation for each practice will be provided only after the practice has agreed to participate and the practice ID and stratification variables are provided to the statistician.

### Patient recruitment

Participating clinicians are asked to invite sequential eligible patients (see Figure 1) consulting with a respiratory tract infection (including common cold, cough, bronchitis or chesty cough, sore throat, tonsillitis, and ear ache). Exclusions (see Figure 1) include children with asthma, pneumonia, and those with ongoing serious disease (cancer, kidney disease, heart disease, etc.) Parents will be asked to provide informed consent, and where a child is deemed capable of consenting, they will be asked to provide consent in addition to the parental consent.

### Data collection

In order to assess possible selection bias we will collect non-identifiable data on all 'potentially eligible patients'. This includes recruited patients as well as those approached but then deemed to be ineligible, those who decline participation, and those not recruited for other reasons (clinician was too busy, etc.) For these patients we will collect: date of consultation, duration of illness, age in years, gender, and presence or absence of the following symptoms: cough, earache, sore throat, runny nose, fever, looks unwell (subjective assessment by clinician). For eligible, consenting patients, we will also collect the patient's and parent's names, contact details (address and phone numbers), and the child's date of birth.

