#### Follow up data collection two weeks after the initial consultation

Most outcomes will be measured by a telephone-administered questionnaire two weeks after the initial consultation. A member of the study team will telephone the parent or guardian of each participant fourteen days after they were enrolled into the study. If the researcher is unable to make contact with the parent on this day they will continue attempting to make telephone contact daily for at least three days. If the researcher is unable to make contact after three days of calling, or if the number given has been found to be incorrect or unavailable, the telephone number will be confirmed with the practice which recruited the patient, and checked with directory enquiries. Parents for whom we are still unable to make contact will be sent a brief questionnaire by post. In order to increase the likelihood of response this questionnaire will deal with only the main outcomes – namely re-consultations and use of antibiotics.

The telephone administered questionnaire will ask about consultations with primary, secondary, and out of hours care providers in the two weeks since enrolment, prescriptions for and use of antibiotics, either at the index consultation or subsequently, use of other medications, satisfaction, usefulness of information provided to them in the initial consultation, level of reassurance, intention to consult with similar illnesses in the future, and questions related to the costs of the illness for the family (time off school/work, etc.) An adaptation of the Patient Enablement Instrument [54] will also be completed over the telephone.

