### Analysis

Statistical analyses will be conducted using SPSS, STATA, and MLwiN. The primary analysis will be intention to treat and will compare the proportion of patients who re-consulted for the same illness during the fourteen days following recruitment, in the intervention and control arms of the study. A two-level logistic model will be fitted to account for individual and practice-level factors.

Secondary outcomes include: proportion reporting having received a prescription for an antibiotic, proportion reporting having used antibiotics, parental enablement, parental satisfaction, parental assessment of the usefulness of any information received in the consultation, perceived reassurance, and the number of consultations for respiratory tract infections over the following year. These will be analysed using either two-level logistic or linear regression models as appropriate.

We will explore whether a three-level model to control for practitioner factors improves the fit of the model for each analysis.

No formal sub-group analyses are planned. However, exploratory analyses will be conducted of the impact of child's age, presenting symptom complex, and socio-economic background (using postcode of residence) on the effectiveness of the intervention.

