The use of a cluster design can lead to selection bias at either the level of cluster or the individual. Practices who agree to take part in the study may find that they no longer wish to participate, leading to attrition bias. This would be of greater concern if there is differential drop-out of practices; for example if practices randomised to the control arm are less likely to recruit (resentful demoralisation). We aim to minimise attrition by maintaining regular contact and providing encouragement to all randomised practices, and will monitor and report on the attrition of clusters. Selection bias can also occur in cluster randomised trials where those who are recruiting participants are aware of the allocation given to their cluster [59]. We are not able to blind practices to their allocation as their use of the booklet within the consultation forms part of the intervention. We have attempted to minimise the risk of selection bias by asking practices to recruit sequential eligible patients, and we are trying to measure any selection bias by asking practices to record non-identifiable data on all 'potentially eligible' patients (i.e. all patients who have been given an information sheet about the study, including those who are deemed ineligible, do not consent, or are not recruited for other reasons).

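### The selection-bias log leaves out index prescribing, and enrolment is not fixed before the treatment decision, so selection on the antibiotic outcome would be largely unseen among logged children

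*Protocol article*

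**What the plan says.** The Patient recruitment section puts enrolment in the hands of the treating clinician: "Participating clinicians are asked to invite sequential eligible patients". The Design issues section states that this clinician knows the arm: "We are not able to blind practices to their allocation as their use of the booklet within the consultation forms part of the intervention". It accepts that this can cause selection bias and names two safeguards, sequential recruitment and a log of potentially eligible children.

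The Data collection section lists what the log holds: "For these patients we will collect: date of consultation, duration of illness, age in years, gender, and presence or absence of the following symptoms", the symptom items being "cough, earache, sore throat, runny nose, fever, looks unwell (subjective assessment by clinician"). A separate list follows for consenting patients (names, contact details, date of birth). Neither list has an antibiotic item.

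The two-week interview asks about "prescriptions for and use of antibiotics, either at the index consultation or subsequently", so the index prescription counts. The Analysis section makes these secondary outcomes: "proportion reporting having received a prescription for an antibiotic, proportion reporting having used antibiotics". The same section makes re-consultation within fourteen days the primary comparison. The follow-up section nevertheless places antibiotic use among the main outcomes, and it is one of the two topics kept in the shortened postal questionnaire.

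**The concern.** One person, aware of the allocation, both decides whether the child enters the sample and produces part of the outcome on which the child is later scored. If enrolment can still be open when the prescribing decision is made, entry to the sample can depend on the outcome. For example, a clinician in an intervention practice who decides to prescribe might not go on to recruit that child. Recruited intervention children would then show less prescribing even if the booklet did nothing.

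The log is the only safeguard of the two that measures selection, and it holds presenting features only. Adjusting for those features, or comparing them between recruited and non-recruited children, does not expose selection on the decision itself. At stake is how far a difference in antibiotic prescribing or use can be credited to the booklet. Antibiotic prescribing is among the stated research questions and in the planned conclusion.

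**Working it through.** **Whether the text allows it.**

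- Pneumonia is an exclusion (Patient recruitment), and the log includes children approached and then found ineligible (Data collection). Some clinical assessment can therefore precede the final enrolment decision.
- No sentence places the enrolment decision before the treatment decision, and none places it after.
- Prescribing is described as collected by parent report at two weeks, from enrolled children only. The patient encounter sheet mentioned under Clinician training is not described. It might record prescribing for recruited children, but the list for non-recruited children does not include it.

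**Size of the possible bias.** The plan gives no figure for this, so what follows is an illustration.

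Inputs:
- b = 0.25, true index prescribing in both arms (approximate figure in the Background section).
- s, the share of prescribed children left out of recruitment in the intervention arm only. The documents give no value; 0.10, 0.30 and 0.50 are assumed.

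Apparent intervention rate = b(1−s) / [b(1−s) + (1−b)]

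- s = 0.10: 0.225 / (0.225 + 0.75) = 23.1%, a spurious difference of 1.9 points
- s = 0.30: 0.175 / (0.175 + 0.75) = 18.9%, a difference of 6.1 points
- s = 0.50: 0.125 / (0.125 + 0.75) = 14.3%, a difference of 10.7 points

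Apparent odds ratio = [b(1−s)/(1−b)] / [b/(1−b)] = 1−s, which is 0.90, 0.70 and 0.50. It does not depend on b.

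**Chance of a falsely significant benefit.** Take the protocol's 524 participants in 60 practices and its intra-cluster coefficient of 0.04. That coefficient is for re-consultation; none is given for prescribing.

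- Mean cluster size: 524/60 = 8.73
- Design effect: 1 + (8.73 − 1) × 0.04 = 1.309
- Effective sample: 524/1.309 = 400, or 200 per arm

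A two-sided 5% normal test of two proportions then favours the booklet with probability about 7%, 31% and 77% for the three values of s, against 2.5% with no selection. With 600 analysed at 10 per practice (design effect 1.36, effective sample 441) the figures are about 7%, 34% and 81%. A larger coefficient for prescribing would lower these chances but would not change the bias.

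The calculation concerns prescribing at the index consultation. The reported outcome also counts later prescriptions, which are not modelled here.

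**The case against.** The strongest reply is that the protocol already names this bias, explains why blinding is impossible, asks for sequential recruitment and adds a log. Presenting features are a defensible choice for such a log because treatment cannot change them. Prescribing, by contrast, is something the intervention aims to change. Four points follow from this, and each has force.

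- **Timing.** A reader might infer that enrolment follows the prescribing decision. The article does not say so. The booklet is meant to be used while treatment options are discussed, which points the other way, and recruitment instructions sit in online training that is not shown. What stands is that the text leaves the order open.
- **Visibility.** A reader might infer that such selection would be wholly invisible. It would not be: selection acting through severity would show in part through fever, illness duration and the rating of how ill the child looks. Only selection beyond those items is hidden.
- **Coverage.** The Design issues section limits the log to children given an information sheet. A child silently passed over is not logged, so a new log item would not reveal that omission.
- **Interpretation.** In the intervention arm, less prescribing among recruited than non-recruited children could be an effect of the booklet, so that contrast cannot separate bias from benefit.

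The omission rates, their direction and their restriction to one arm are also assumptions with no support in the documents. What survives is narrower: the log has an explicit list, its stated purpose is to assess selection bias, and it lacks the variable through which selection would act most directly on an outcome that the protocol itself treats as important.

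**Conclusion.** The point holds as a modest, inexpensive improvement. Among logged children, selection on the prescribing decision beyond what the listed presenting features capture would be largely unseen, and the text does not close off that route by fixing enrolment first. It concerns the secondary antibiotic outcomes. A reader might extend it to the primary outcome, but the documents give no direct mechanism for that; any effect on re-consultation would be indirect.

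The odds ratios in the illustration show how selection would pass into the result at assumed omission rates. They are not estimates of bias in this trial, and nothing in the documents shows that such selection will occur.

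**What to change.** 1. In the process training for both arms, instruct clinicians to give the information sheet and record the enrolment decision before the treatment decision.
2. Add one non-identifiable item to the log for every child on it: antibiotic prescribed at this consultation (none, delayed, immediate).
3. As a sensitivity analysis for the antibiotic outcome, compare index prescribing between arms over all logged children who met the eligibility criteria, recruited or not, leaving out those deemed ineligible. This comparison does not depend on who was recruited after being approached.
4. Report prescribing in recruited and non-recruited children within each arm, and state that in the intervention arm a difference may reflect the booklet as well as selection.

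The cost is one tick-box on an existing form, a sentence of training, a table, and a few seconds per logged child. The item has to be collected as children are logged: because the log is non-identifiable, it could not readily be recovered later for non-recruited children.

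The remedy has limits. The sensitivity analysis dilutes any true effect, since non-recruited intervention children may not have received the booklet. It still relies on the clinician's judgement of eligibility, and it says nothing about children never given an information sheet.

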#### Follow up data collection two weeks after the initial consultation

Most outcomes will be measured by a telephone-administered questionnaire two weeks after the initial consultation. A member of the study team will telephone the parent or guardian of each participant fourteen days after they were enrolled into the study. If the researcher is unable to make contact with the parent on this day they will continue attempting to make telephone contact daily for at least three days. If the researcher is unable to make contact after three days of calling, or if the number given has been found to be incorrect or unavailable, the telephone number will be confirmed with the practice which recruited the patient, and checked with directory enquiries. Parents for whom we are still unable to make contact will be sent a brief questionnaire by post. In order to increase the likelihood of response this questionnaire will deal with only the main outcomes – namely re-consultations and use of antibiotics.

The telephone administered questionnaire will ask about consultations with primary, secondary, and out of hours care providers in the two weeks since enrolment, prescriptions for and use of antibiotics, either at the index consultation or subsequently, use of other medications, satisfaction, usefulness of information provided to them in the initial consultation, level of reassurance, intention to consult with similar illnesses in the future, and questions related to the costs of the illness for the family (time off school/work, etc.) An adaptation of the Patient Enablement Instrument [54] will also be completed over the telephone.

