**Methods/Design:**

This will be a cluster randomised controlled trial. General practices will be randomised to provide parents consulting because their child has an acute respiratory tract infection with either an interactive booklet, or usual care. The booklet provides information on the expected duration of their child's illness, the likely benefits of various treatment options, signs and symptoms that should prompt re-consultation, and symptomatic treatment advice. It has been designed for use within the consultation and aims to enhance communication through the use of specific prompts. Clinicians randomised to using the interactive booklet will receive online training in its use. Outcomes will be assessed via a telephone interview with the parent two weeks after first consulting. The primary outcome will be the proportion of children who re-consult for the same illness episode. Secondary outcomes include: antibiotic use, parental satisfaction and enablement, and illness costs. Consultation rates for respiratory tract infections for the subsequent year will be assessed by a review of practice notes.

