### Main research questions

Our main aim is to determine whether the pragmatic use of this intervention can result in a reduction in the proportion of children who re-consult during the same illness episode. We will also examine the impact that use of this intervention has on: antibiotic prescribing and use, parental satisfaction, parental enablement, intention to consult with a similar illness in the future, illness costs, and consultation rates for RTIs over the following year. In this paper we describe the study protocol.

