### Sample size estimation

The primary outcome is re-consultation for the same illness episode. In order to show a reduction in the proportion of children re-consulting from 20% to 10%, with 80% power, and a 5% significance level, we would require 438 participants for an individually randomised trial. From a previous study of upper respiratory tract infections in children [4], we calculated an intra-cluster coefficient of 0.04 for re-consultation rates. Using 60 clusters (practices) we would need 524 participants to have the same power as an individually randomised trial. To allow for loss to follow-up and missing data we have decided on a target recruitment of 600 participants, 10 from each practice.

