## Conclusion

This study aims to evaluate the effect of a booklet developed specifically for use within consultations involving children with RTIs, on re-consulting for the same illness episode and antibiotic prescribing. We will determine whether changes in antibiotic use and re-consultation are achieved at the expense of patient satisfaction, and will determine whether the interactive booklet enhances patient enablement. We will evaluate the effect on medicalisation over the subsequent year. If this intervention is found to be effective, even small changes for the commonest acute consultation could have major effects on help seeking behaviour and free up consultations in primary care for other conditions. If not effective, resources spent on developing, printing, and distributing leaflets and booklets on respiratory tract infections in children can be re-directed, and the research agenda can be re-focussed. We believe that this is the first evaluation of the use of written material on respiratory tract infection in children during the consultation.

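### As described, the postal follow-up form leaves out antibiotic prescription, which the plan analyses as an outcome separate from antibiotic use

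*Protocol article*

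**What the plan says.** The protocol article's section on two-week follow-up describes two instruments.

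- **Telephone questionnaire.** Among other items it asks about "prescriptions for and use of antibiotics, either at the index consultation or subsequently". Prescription and use are named separately.
- **Postal questionnaire.** After repeated calls and checks of the number, "Parents for whom we are still unable to make contact will be sent a brief questionnaire by post". To raise the response rate, "this questionnaire will deal with only the main outcomes – namely re-consultations and use of antibiotics".

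The Analysis section then lists as separate secondary outcomes the "proportion reporting having received a prescription for an antibiotic, proportion reporting having used antibiotics". The Main research questions section also names both: "antibiotic prescribing and use, parental satisfaction, parental enablement".

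**The concern.** The word *only*, followed by a two-item list, reads as a closed list, and prescription is not on it. The telephone description in the next paragraph names prescription and use side by side, so the text treats them as different things at the point where data collection is specified.

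Use cannot replace prescription, because a prescribed antibiotic may not be taken. That difference is presumably why the plan keeps two outcomes. If the postal form does not ask about prescription, the item is lost at collection and no analysis plan can recover it.

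Postal families are by definition those whom several days of calls did not reach, so they may differ from the rest. Prescribing is also prominent among the outcomes: the Discussion and Conclusion pair it with re-consultation when they state what the trial is about. By the form's own criterion of keeping the main outcomes, prescription would be expected on it.

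**Working it through.** **Step 1. Is the item collected anywhere else?** The relevant sections of the protocol article, side by side:

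| Section | Prescription | Use |
|---|---|---|
| Two-week follow-up, telephone | named | named |
| Two-week follow-up, postal | not named | named |
| Data collection (at enrolment) | not named | not named |
| Follow up data one year after the consultation | not named (consultation length and counts only) | not named |
| Analysis | separate parent-reported outcome | separate parent-reported outcome |

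The Clinician training section mentions a patient encounter sheet but lists no prescription item for it. As described, the telephone interview is therefore the only source of the prescription outcome.

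**Step 2. How large could the loss be?** The article gives no postal share and no figure for this outcome, so the following is a range under assumptions.

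Inputs from Sample size estimation: 20% v 10%, 5% significance, 60 practices, intra-cluster coefficient 0.04, 524 participants. Assumptions: 524 children are followed up in all; 0% to 20% of them reply by post; the coefficient of 0.04 and the 20% v 10% difference, both stated for re-consultation, are borrowed for prescription.

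Formulas:

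- Children with a prescription value: N = 524 × (1 − postal share)
- Mean cluster size: m = N / 60
- Design effect: DE = 1 + (m − 1) × 0.04
- Effective sample size: N / DE, with n = half of this per arm
- Power = Φ{[0.10 × √n − 1.96 × √(2 × 0.15 × 0.85)] / √(0.20 × 0.80 + 0.10 × 0.90)}

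Reference case, no postal replies: m = 524 / 60 = 8.73; DE = 1 + 7.73 × 0.04 = 1.309; effective size = 524 / 1.309 = 400; n = 200. Power = Φ[(1.414 − 0.990) / 0.5] = Φ(0.849) = 80.2%, which matches the 80% that the plan states for 524. The formula has no continuity correction because that is the basis on which 524 gives 80%.

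| Assumed postal share | N with prescription | Effective size | Power, 20% v 10% |
|---|---|---|---|
| 0% | 524 | 400 | 80.2% |
| 5% | 498 | 385 | 78.7% |
| 10% | 472 | 370 | 77.1% |
| 15% | 445 | 354 | 75.3% |
| 20% | 419 | 338 | 73.3% |

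**Step 3. What the table does not show.** It measures loss of precision only. Any bias depends on how postal families differ between arms, and the article gives no information on that.

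**The case against.** The strongest reply is that the form is not reproduced. The sentence names topics, not items, and the other topic is just as condensed: re-consultations stands for what the telephone form splits into primary, secondary and out-of-hours contacts. An article commonly leaves exact items to the full protocol.

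The article also uses antibiotic use as a broad term. The abstract says "Secondary outcomes include: antibiotic use, parental satisfaction and enablement, and illness costs", although prescription is an outcome too. The Conclusion names antibiotic prescribing as a target and then continues: "We will determine whether changes in antibiotic use and re-consultation are achieved at the expense of patient satisfaction". On that usage the postal form may well ask about prescriptions. This part of the objection stands, and it limits the point to what the text implies. It does not remove the point, because the broad usage is in summary passages, whereas the follow-up section separates the two terms in adjacent paragraphs.

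A second reply is that the short form is a disclosed trade-off to raise response, and that satisfaction, enablement and reassurance are telephone-only as well. This is fair for those outcomes. It is weaker for prescription, because the form already asks about antibiotics and one more tick-box adds little burden.

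Several stronger readings are tempting but are not supported:

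- **That prescription definitely cannot be scored for postal families.** The article never says that the item is left off or that these families are excluded from the prescribing analysis.
- **That the effect estimate could be wrong by as much as the whole postal share.** Such bounds treat prescription as wholly unknown in these children. Their antibiotic use is recorded, so the uncertainty lies mainly in reported non-users.
- **That the gap between 600 and 524 forecasts the loss after postal follow-up.** The article says "To allow for loss to follow-up and missing data we have decided on a target recruitment of 600 participants"; 524 is a required sample size, not a prediction of follow-up.
- **That a gap between the prescription and use results would mislead.** No comparison of the two effects is planned, and telephone responders have both items, so any gap can be examined within one group.

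**Conclusion.** The point holds as a minor one. As described, prescription is not collected from families followed up by post, although it is a separate secondary outcome with no other described source. Its denominator would be smaller than that for re-consultation and use, and possibly selected.

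The size cannot be determined from the article. Under the assumptions in the working, power falls by about 1.5 to 7 percentage points (80.2% to 78.7% at a 5% postal share, to 73.3% at 20%). That is modest, and the primary outcome is not affected. The conclusion rests on reading the postal sentence literally; if use was meant to include prescription, only the wording needs to change.

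**What to change.** Add one yes/no item to the postal form: was an antibiotic prescribed for your child, at the index consultation or since? Re-consultation, prescription and use would then all be sought from the same families. If the form already asks this, reword the sentence in the two-week follow-up section so that it names prescription as well as use.

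The cost is one tick-box and a marginally longer form, with at most a slight effect on postal response. If only the wording changes, there is no cost.
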